### Outcome measures

As mentioned above, the primary objectives of this study are to establish the impact of the ECED project on early childhood development outcomes. The results are also to inform the pathways of impact and obtain greater insight into the patterns and correlates of child development in Indonesia. In order to understand the pathways not just at a household, but also a community level, the evaluation makes use of six questionnaires covering the state of children’s development and the context in which children develop. At baseline, there were six separate questionnaires: a child questionnaire that included child tasks, caregiver questionnaire, household head questionnaire, village midwife questionnaire, posyandu (integrated child health services clinic) questionnaire and a village head questionnaire. The midwife and posyandu were included for the baseline data collection as these are publicly provided health services targeted at young children and they are often the most common form of ECED services in a village. For the midline data collection, the midwife and posyandu questionnaires were replaced with a dusun level questionnaire related to project services (in treatment areas), and a village level questionnaire related to ECED services (in treatment and control areas). The midwife and posyandu questionnaires were dropped mainly for cost reasons. While the information from these service providers was valuable, the research team found it more beneficial to gather data on project implementation and more comprehensive information on ECED service availability and provision, and it was not feasible to have four village level questionnaires in the midline data collection.

#### Instrument development and piloting

Access to services, service utilization, asset inventory, dwelling attributes and consumption history by the household were collected using a series of questions that were previously constructed for the Indonesian Family Life Survey (IFLS), a renowned panel study focusing on demographic, poverty and health measures. The child and caregiver questionnaires include several internationally-recognized standard scale instruments and anthropometric measures. We also collected information about the child’s development and health history from the parent/caregiver. None of the standard tools used to measure childhood development had been applied in Indonesia before. As such, the instruments had to be translated and adapted to the Indonesian culture and circumstances, and the study design meant that some of the standard measures of child development needed to be amended.

#### Early Development Instrument (EDI)

The Early Development Instrument (EDI) is generally completed for each child in the kindergarten classroom by the child’s teacher. In Indonesia, very few children attend school at the age of 4 years, particularly in poor regions, and thus the first variation was that the EDI was to be completed by an interviewer with the caregiver of the child. The full EDI includes a core checklist of 104 items, combining five major areas of child development and 16 sub-domains. However, the EDI also comes in a short form with 48 items. Due to the number and length of instruments being used in the impact evaluation and concern for respondent burden, it was decided to use the short form of the EDI from inception. It is acknowledged that the author of the EDI does not recommend the use of the short form EDI prior to analyses of all the items by piloting the full EDI in a country first [34].

#### Strengths and Difficulties Questionnaire (SDQ)

The Strengths and Difficulties Questionnaire (SDQ) [35], which is also an informant-based assessment of a child, is also used internationally. The SDQ had already been translated to Indonesian by Wiguna and Hestyanti [36]; however, no validation data for the translated version is published.

#### Dimensional Change Card Sort (DCCS)

As a test of executive cognitive functioning, we included the Dimensional Change Card Sort (DCCS) task [37,38]. This task involves a child sorting cards with pictures that vary by shape and color into two groups according to one dimension (by shape), and then switching to sorting them by the other dimension (by color). Traditionally the colors are red and blue and the shapes represent a rabbit and a boat. For the purposes of the ECED impact evaluation we changed the shapes to a motorbike and a cat as these are more familiar to children in Indonesia.

#### Child tasks

Various tasks similar to those used in the Ages and Stages Questionnaire (ASQ) [39] and an instrument used in the Philippines for another World Bank project [31] were also included in the ECED impact evaluation. These included fine motor skills tasks (threading string through a bead), gross motor skills (sitting through to walking backwards, hopping on one foot and throwing a ball overhead), cognitive assessment (by drawing a circle, a person and a house), and expressive and receptive language (by identifying pictures and parts of their body).

#### Content validity and piloting of the instruments/questionnaires

Content validity was established over a period of 4 years from 2006 to 2009 involving meetings, focus groups and various pilots in the field. Initial meetings were held with staff from the Government of Indonesia who had expertise in early child development. Translators were present at these initial meetings. No modifications to the instruments were made at this stage other than the inclusion of a set of questions regarding the child’s knowledge of Muslim prayers and religious practices. This version of the instrument was piloted in a mix of poor urban and rural villages near Majalengka (West Java) in March 2007, gaining a total of eight completed questionnaires.

The pilot revealed difficulties in the translation of response ranges (that is, ‘sometimes agree’ through to ‘sometimes disagree’) with a distinct preference for simple yes or no answers. The interviewers were government staff from the Department of Early Childhood (PAUD) within the MoNE and one experienced fieldworker who had worked on the IFLS and other significant surveys in Indonesia. There was much debate among the interviewers regarding the five ordered response categories and if it was possible to generate a range from the respondents or not, with the expected response in the Indonesian language being ‘can’ (bisa) or ‘cannot yet’ (tidak bisa). In addition, the interviewers were concerned about a strong social desirability response bias displayed by the child’s caregivers. After this pilot testing, the study team added a series of child tasks, fieldworker observations and repeat questions within the instrument suite to try to counter the social response bias and increase our ability to assess reliability. Further translations and back-translations were undertaken to improve the understanding/interpretability of the ranged response.

In September 2007, this amended full suite of instrumentation was piloted in Subang (Central Java) with 26 households. Similarly to the previous pilot, there was still difficulty with the ranged response categories. In addition, questions that required some degree of subjectivity in the answer seemed to be very difficult for the respondents (for example, ‘How would you rate your child’s overall social/emotional development?’). Such questions required greater guidelines and training for the interviewers.

#### Baseline pilot study

After another series of modifications, the instruments were again back-translated to English for checking before a final and comprehensive pilot. This baseline pilot was conducted in January 2009 in Yogyakarta and Kebumen in Central Java by the survey firm, Bina Karya, which was hired by the MoNE to carry out the baseline survey. This pilot surveyed 200 households (children, caregivers and household heads), 20 midwives or posyandu (integrated child health services clinic) heads and ten village heads. The purpose of this pilot was primarily to validate the instruments, especially for the children, to ensure that the instruments captured a range of child capabilities and did not pose ceiling or floor effects. Secondly, the pilot was to test the comprehension of survey questions by respondents and the overall flow of the questionnaire, and serve as an opportunity for Bina Karya to practice the logistics of implementing the survey.

### Quality control

#### Project quality control

Frequent project coordination meetings with government were and still are being conducted by the World Bank as standard practice with any loan to a country. In addition, the World Bank’s project management team based in the Indonesian office generally organizes two annual formal review sessions, each producing an *aide*-*mémoire* which documents the project’s accomplishments, challenges and proposed remedies. The project management team is in daily contact with the MoNE and makes frequent visits to oversee project implementation.

#### Baseline survey quality control

Fieldwork training took place in March 2009 over 5 days in three locations throughout the country: Yogakarta (Central Java), Lampung (Sumatra) and Mataram (Lombok). Training covered the details of the fieldwork manual including protocols for obtaining consent, ensuring confidentiality, how to probe effectively and questionnaire content. The training also included a module for data entry staff to become familiar with the data entry program (the manual and program was developed by World Bank staff), and a field practice with live respondents.

Field teams used paper questionnaires but data were entered shortly after enumeration as data editors were co-located with enumerators during fieldwork. Baseline fieldwork took place from March to June 2009. Each field team consisted of five to six fieldworkers and a team supervisor. It was the supervisor’s responsibility to: gain support/permit from the village head, conduct the village level instruments (village head, midwife and posyandu), check all surveys for completeness and quality before leaving the village, and keep track of participation.

Baseline survey quality control was carried out by a combination of staff from the survey firm’s leadership team, the MoNE and the World Bank. Quality control during survey implementation included attending the pilot and training, frequent visits to the field to accompany supervisors and enumerators during questionnaire administration, and observing the process of data editing and entry. Survey firm supervisors and several MoNE and World Bank staff also revisited households to verify data collected by enumerators. Subsequent to fieldwork, MoNE and World Bank staff were involved in observing the second data entry and cleaning process which took place at Bina Karya offices in Jakarta. Throughout the entire survey effort, MoNE and World Bank staff provided feedback and recommendations to Bina Karya staff regarding measures to improve fieldwork management, interviewing quality, data entry processes, and clarifying instrument content.

Despite these quality checks and processes there were still problems with data quality. As an example, it was found that one fieldwork team entirely made up their data. Once this was discovered a new fieldwork team went back out to those villages and the data were collected properly.

#### Midline survey quality control

Many of the same procedures and protocols for the baseline were repeated for the midline data collection, with some exceptions. First, some questionnaire content was altered to reflect the baseline experience, for example, questions that were found to be ineffective, showing little variation or proving not to be understood by respondents were revised or dropped. The team also added a different suite of questionnaires at the village and dusun levels related to project implementation and overall ECED service provision and availability. Second, the MoNE implemented the survey differently. The MoNE recruited a team of five highly experienced survey consultants to lead the survey, along with an event organizing firm, which handled all administration and logistics of the survey, but not survey content or quality. The lead consultants were responsible for recruiting all fieldworkers and delivering high quality data.

Because of the changes to questionnaire content and implementing structure, two pilots were conducted prior to midline survey. The first pilot was conducted in Lombok in April and May 2010, and the second in Subang (West Java) in June 2010. The purpose of the pilot was similar to that of the baseline pilot, with a focus on the new questionnaires about ECED service provision and project implementation. The team conducted two pilots because the objective of the first was to test questionnaire content and served to refine the questionnaires, whereas the second pilot was to practice logistics of survey administration and get final estimates on survey administration time.

Midline survey training began with a 2-day workshop for district coordinators in Jakarta, followed by 7 days of fieldworker training in Bandung in late June/early July (thus all fieldworkers were trained together). Midline data collection took place in July and August 2010. Midline data collection quality control was largely similar to the baseline with survey team leadership, MoNE and World Bank staff making frequent field visits throughout the duration of the fieldwork to verify data collected and entered, accompany fieldworkers during interviews, and offer coaching and feedback regarding questionnaire administration and content. As with the baseline, a first round of data entry took place in the field with the second round of data entry in Jakarta.

### Planned analyses

As noted above, there are several hypotheses under the trial. One of the risks when collecting a large set of outcome variables is to highlight false positives in the final analysis, that is, significant coefficients are identified in the final analysis when, in fact, these could be due to natural randomness. To reduce this risk, for each hypothesis below we list (in bullets) which outcome variables we will use to test our research hypotheses. We believe that by limiting the analyses to a parsimonious set of variables defined *ex ante*, the risk of false positives is greatly reduced. The hypotheses under the trial are whether the ECED program has led to:

1) Greater access to ECED services

• The number of children aged 0 to 6 years in the village/ECED centers in the village

2) Higher participation rate in ECED services

• The fraction of children that attend an ECED service at least once a week by age five years

3) Higher enrolment rate in school at earlier ages

• The fraction of children aged 6 to 8 years that enrolled in primary school at the age of 6 years. (For children aged 7 and 8 years, their age of enrolment will be inferred by the grade they are in at the time of the survey)

4) More ‘school ready’ children

• The summary values of the EDI in the domains of physical health and well-being, social competence, emotional maturity, language and cognitive skills, communication skills, and general knowledge

• Mean score on the SDQ in the areas of emotional symptoms, conduct problems, hyperactivity/inattention, peer relationship problems and pro-social behavior

• The average numbers of stages children pass on the DCCS task (there are three stages)

• The fraction of tasks children can perform in the areas of gross motor skills, fine motor skills, language skills, cognitive skills and socio-emotional skills

5) Higher community awareness about the importance of ECED

• Parental knowledge about the location of key ECED services in the village

6) Higher persistent breastfeeding rates, improved nutrition and improved early childhood stimulation.

• Average number of months of exclusive breastfeeding for children when they were below the age of 6 months

• Height-for-age z-score, weight-for-height z-score

• Number of activities children engaged in last week (out of book reading, storytelling, drawing, music, playing with toys and helping in household chores) and fraction of children that play outside

The first steps in the analysis will be to further validate the instruments used. This will be undertaken by assessing floor and ceiling effects, correlates between measurements, and investigating gradients with socio-economic indicators as well as with age and gender. These analyses will also provide a unique snapshot of the early development of a large cohort of Indonesian children [40].

Having two control groups, an experimental and a matched control, is an unusual feature of this evaluation. Usually an experimental design would be the first choice, and the entire sample would be allocated to this. This rule of thumb was not followed for this evaluation because the effect of the intervention is expected to depend on the duration of exposure to the project. The largest measurable impact is thus expected for children that live in Batch 1 villages at the end of the project. Measuring this impact is the main objective of the evaluation. The randomized control sample is of limited value in estimating this impact as it will have already received the intervention by the end of the project. The matched control sample, on the other hand, will never receive the intervention. Using the observations from the Batch 1 villages and matched control villages, the impact of the project can be estimated using:

(1)$$Y_{\mathrm{ijt}}=\alpha_{t}+X_{\mathrm{ij}0}\beta_{t}+\delta_{t}T_{j}+\epsilon_{\mathrm{ijt}}$$

Where *i* denotes the child, *j* the village, and *t* = 1,2 indicates the time of the baseline, midline and endline surveys. *X* is a vector of village and child baseline characteristics, and *T* indicates whether the village received the project (*T* = 1 for Batch 1 villages and *T* = 0 for matched control villages).

This estimate is a valid impact estimate under the assumption that the outcomes at endline, given baseline characteristics, would be equally distributed in the Batch 1 villages and matched control villages in the absence of the intervention. This assumption cannot be tested at baseline but can be tested at midline. At midline, the averages observed in the randomized control sample of Batch 3 villages are a valid estimate of the expected outcomes in Batch 1 villages in the absence of the intervention. Whether these estimates are equal to those of the matched control sample can be tested by estimating:

(2)$$Y_{\mathrm{ij}1}=\gamma +X_{\mathrm{ij}0}\theta +\mathrm{\pi M}C_{j}+\epsilon_{\mathrm{ij}}$$

An estimate of *π* that is not significantly different indicates that the matched control sample would have been a valid control group at midline when using the sample of matched control (*MC* = 1) and randomized control villages (*MC* = 0). If this is true, it also increases the ‘comfort factor’ of making this assumption at endline. If not, it provides an indication of the direction in which the estimates from (1) will be biased.

At midline, the experimental design makes it possible to estimate the average treatment effect of the first 18 months of intervention with minimal assumptions. Batch 3 villages will still be a valid control group. Using data from Batch 1 (*T* = 1) and Batch 3 (*T* = 0), the average treatment effect can be estimated by:

(3)$$Y_{\mathrm{ij}1}=\rho +X_{\mathrm{ij}0}\varphi +\vartheta T_{j}+\epsilon_{\mathrm{ij}}$$

Outcomes will be indicators of child development and utilization of early childhood development services. The latter is of interest as the projects aims to increase child development through improved access to early childhood development services. Considering both types of outcome variables provides an opportunity to evaluate the pathways of impact.

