**Methods/Design:**

The study is being conducted across nine districts. The baseline survey contained 310 villages, of which 100 were originally allocated to the intervention arm, 20 originally allocated to a 9-month delay staggered start, 100 originally allocated to an 18-month delay staggered start and 90 allocated to a matched control group (no intervention). The study consists of two cohorts, one comprising children aged 12 to 23 months and the other comprising children aged 48 to 59 months at baseline. The data collection instruments include child observations and task/game-based assessments as well as a questionnaire suite, village head questionnaire, service level questionnaires, household questionnaire, and child caretaker questionnaire. The baseline survey was conducted from March to April 2009, midline was conducted from April to August 2010 and endline conducted early 2013. The resultant participation rates at both the district and village levels were 90%. At the child level, the participation rate was 99.92%. The retention rate at the child level at midline was 99.67%.

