In Indonesia, in 2004, there were four different kinds of educational programs available for children aged 0 to 6 years: kindergarten (47,696 programs), Islamic kindergarten (1,560), playgroups (5,169) and childcare centers (1,789) [28]. Of the 28 million children aged 0 to 6 years in Indonesia, only a small minority participated in early childhood education services prior to primary school, which children are expected to start at the age of 7 years. Enrolment was estimated to be only 8% whereas the global average enrolment rates for low income countries stood at 24% [28]. In 2004, 85% of children in the poorest quintile (measured using household per capita consumption) were not participating in any kind of early childhood programs. In addition, children from the poorer villages start school later, complete fewer years of schooling, and have higher dropout and repetition rates [22].

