### Project timetable

The timeline of impact evaluation milestones are presented in Table 1.

**Table 1 T1:** Timeline of impact evaluation milestones

**Impact evaluation milestones**	**Anticipated**	**Actual**
Sample size calculations	December 2006	December 2006
Randomization of 20 villages/districts to T and C status	March to July 2007	March to July 2007
Selection of matched controls	March to July 2007	March to July 2007
Discovery of randomization compliance issues	N/A	December 2008
Batch 1/treatment receives block grants	February 2008	November to December 2008
Batch 1/treatment opens services	December 2008	March 2008 to December 2009
Baseline survey	January 2008	March to June 2009^a^
Batch 3/randomized control receives block grants	May 2009	November 2009 to June 2010
Batch 3/control opens services	July to August 2010	January 2010 to present
Midline survey	March 2010	July to August 2010
Endline survey	Planned for early 2013	February to July 2013

^a^Fieldwork in most districts took place in March and April 2009, with some exceptions. Data collection in Lombok went into June due to some delays in paying enumerators and because the sample was over double that of the other districts. Because it was discovered that data were falsified in Sarolangun and Bengkulu, the World Bank hired a team to re-administer surveys in Bengkulu in June 2009 and in Sarolangun from October to December 2009. *C* control, *T* treatment.

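### Hypothesis 3 counts six-year-olds who can still enrol at six as not having done so, which understates early enrolment and modestly dilutes the between-arm difference

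*Protocol article*

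**What the plan says.** Planned analyses lists, for each hypothesis, the outcome variables fixed in advance to limit false positives. Hypothesis 3 (earlier school enrolment) has one: "The fraction of children aged 6 to 8 years that enrolled in primary school at the age of 6 years". For ages 7 and 8 it adds that "their age of enrolment will be inferred by the grade they are in at the time of the survey". It gives no rule for a six-year-old who is not yet in school and does not state the survey round.

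The section on the Indonesian context describes primary school as something "which children are expected to start at the age of 7 years". The abstract gives two panel cohorts, "one comprising children aged 12 to 23 months and the other comprising children aged 48 to 59 months at baseline". On timing, Baseline survey quality control says "Baseline fieldwork took place from March to June 2009", and the footnote to Table 1 adds later exceptions. Table 1 dates the endline "February to July 2013".

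**The concern.** A child who is 6 and not yet in school has not failed to enrol at 6; the year is unfinished. With 7 as the usual entry age, such children will be common. Read literally, the definition puts them in the denominator as non-events. This can only lower the fraction, and if it acts alike in both arms it also shrinks the difference between them. It also makes the result depend on fieldwork timing, because the month of interview decides how many children are 6 and how far through that year they are.

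A second, smaller point concerns the upper limit. It suits a three-year follow-up, but on the Table 1 dates part of the older cohort has turned 9 by endline and falls outside the window.

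**Working it through.** **Inputs.** Older cohort 48 to under 60 months and younger cohort 12 to under 24 months at baseline (abstract). Baseline March to June 2009, mostly March-April. The Table 1 footnote says Lombok ran into June, Bengkulu was re-surveyed in June 2009 and Sarolangun in October to December 2009. Midline July-August 2010 and endline February to July 2013 (Table 1). Assumptions: ages uniform within cohort, interviews spread evenly over the endline months, equal cohort sizes.

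**1. The plan's own figure.** Sampling procedures expects the older cohort to be around 7 at endline. With the nominal gap of 36 months: (48 + 36)/12 = 7.0 to (60 + 36)/12 = 8.0 years. Reproduced. No older-cohort child would then be 6 or 9, and the younger cohort would be 4.0 to 5.0.

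**2. Actual dates.** March-June 2009 to February-July 2013 is a gap of 44 to 52 months. Older cohort: (48 + 44)/12 = 7.7 to (60 + 52)/12 = 9.3 years. Younger cohort: (12 + 44)/12 = 4.7 to (24 + 52)/12 = 6.3 years.

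**3. Shares outside or only just inside the window.** For a gap of g months, the share of the older cohort aged 9 or more is (60 + g − 108)/12, floored at 0. The share of the younger cohort aged 6 is (24 + g − 72)/12, which is the same number.

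| Baseline | Feb | Mar | Apr | May | Jun | Jul | Mean |
|---|---|---|---|---|---|---|---|
| March 2009 | 0 | 0 | 8% | 17% | 25% | 33% | 13.9% |
| April 2009 | 0 | 0 | 0 | 8% | 17% | 25% | 8.3% |
| June 2009 | 0 | 0 | 0 | 0 | 0 | 8% | 1.4% |
| Oct-Dec 2009 | 0 | 0 | 0 | 0 | 0 | 0 | 0 |

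March-April baselines average 11.1%; baselines spread evenly over March-June average 6.9%.

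**4. Weighting by district.** Assume 30 villages in each of eight districts and 70 in Lombok (8 × 30 + 70 = 310). Six districts have March-April baselines (180 villages), Lombok is spread over March-June, Bengkulu is June and Sarolangun is zero:

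(180 × 11.1% + 70 × 6.9% + 30 × 1.4% + 30 × 0) / 310 ≈ 8.2%.

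**5. Share of the denominator.** Let s be the share from step 3 or 4. The window holds s of the younger cohort (all aged 6) and 1 − s of the older cohort (aged 7 or 8). With equal cohorts, six-year-olds make up w = s/(s + 1 − s) = s: about 8%, or about 11% for March-April baselines. If all village children aged 6, 7 and 8 contributed equally, w = 1/3.

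**6. Effect on the outcome.** Let p be the true fraction enrolling at 6 and q the share of six-year-olds' eventual age-6 enrolments already visible at interview. Then observed fraction = p × (1 − w(1 − q)). With w and q equal in both arms, the difference shrinks by the same factor. The article gives neither p nor q, so take p = 0.30 as an assumption and let q run from 0 to 1:

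- w = 0.11: observed 0.267 to 0.30.
- w = 1/3: observed 0.20 to 0.30.

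The relative loss is at most w, reached only when q = 0.

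**7. Midline, if used.** March-June 2009 to July-August 2010 is 13 to 17 months. The older cohort is then (48 + 13)/12 = 5.1 to (60 + 17)/12 = 6.4 years. No panel child is yet 7.

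**The case against.** Several arguments limit the point.

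- **Midline.** A reader might infer that the randomized midline comparison for this hypothesis rests wholly on incompletely observed children. That would be so if it were run, but nothing in the article assigns hypothesis 3 to midline. Sampling procedures places school outcomes at endline, and the text after equation (3) names child development and use of early childhood services. Only the unstated survey round remains.
- **Nine-year-olds.** A reader might infer that excluding them also understates enrolment, or that the upper limit should simply go. Neither follows. The loss has no fixed direction, so it costs precision only. Entry age is inferred from grade, and the section on the Indonesian context reports more repetition in poorer villages. A repeater looks like a late starter, with more chance of error at each further grade, so an upper limit is defensible.
- **Population.** The definition does not say panel children. The Discussion raises collecting data on all village children through schools. Under that reading 8 is an ordinary cut-off, so the one-third figure and the loss of nine-year-olds cannot both apply.
- **False positives.** Allocation and matching were within district, and nothing suggests that interview month differed by arm. The error is then non-differential and conservative.
- **Level of detail.** A condensed article leaves much to the full analysis plan. That does not dispose of the point, because the age window is stated here and it is the stated window that misclassifies six-year-olds.

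**Conclusion.** The definition is wrong as written for children still aged 6 at interview. It lowers the fraction, ties it to interview month and pulls the between-arm difference towards zero. In the endline panel the dilution is at most about 8%, or about 11% where baselines were in March-April 2009. If all village children aged 6 to 8 were used equally, it is at most about a third. These are upper bounds, reached only if none of the six-year-olds' later age-6 enrolments is visible at interview. They rest on uniform ages, evenly spread interviews, equal cohort sizes and the village weights in step 4. Interview timing alike in the arms is also assumed; on that footing no false positive arises.

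The exclusion of panel children aged 9, about 8-11% of the older cohort, is a secondary matter of precision. The point affects one of six hypotheses. It is worth correcting because the outcome was fixed in advance and the correction is cheap.

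**What to change.** Define the hypothesis 3 denominator as children who have passed their seventh birthday at interview, or keep six-year-olds and treat them as censored. State that the outcome is assessed at endline. Keep the upper limit in the main analysis, and add panel children aged 9 in a sensitivity analysis, noting that inference from grade misclassifies repeaters more often at older ages.

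This takes one or two sentences. In the panel, dropping six-year-olds removes about 8-11% of the denominator. Adding the nine-year-olds would roughly replace them, since the two shares are equal when the cohorts are. If all village children are used, the restriction removes about a third of the denominator, and treating six-year-olds as censored avoids discarding them outright.
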